#### Fasting blood glucose level

3.10.6

After a 10 to 12 hour fast, blood glucose levels are measured in serum from the same blood samples drawn for lipid profile, using the hexokinase/G-6-PDH technique.

### Statistical analysis

3.11

An analysis will be made by intention to treat. The description of the categorical variables will be made by means of absolute and relative values. Quantitative variables that present a normal distribution in Shapiro Wilk's test will be reported as mean and standard deviation, otherwise the median and interquartile range will be presented. The comparison of the basal characteristics of the study groups (intervention and control) will be done using the ratio comparison test (Chi-square or Fischer's exact test) and the Student's t-test or Mann-Whitney's U-test.

Quantitative outcome variables will be contrasted through paired t-tests or Wilcoxon tests for quantitative variables, methods of longitudinal data analysis will also be explored and for categorical ones the Mc Nemar test will be used. Statistical significance will be considered for all hypothesis tests when the *P* value is less than .05.

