### Sample size

3.3

The simple size was calculated considering the following parameters: an expected difference in the study outcomes (overweight, obesity, and alteration of the lipid profile) of 20% between the intervention group and the control group; a power of 90%, an alfa of 5%, an intervention group/control group ratio of 1:1, and a 20% adjustment for losses to follow-up, resulting in a sample of 270 participants (n = 135 intervention and n = 135 control group). The OpenEpi software was used for the calculation. Since this is a pilot study and considering the feasibility, the research team decided on a sample size of 150 participants (n = 75 intervention group and n = 75 control group).

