### Recruitment

3.5

For recruitment, a study nurse in charge of enrollment will contact by phone the 217 successful participants of the third re-contact, explain the objective of the study and inquire about the interest to participate; if there is a positive response, inclusion and exclusion criteria will be verified. A list of eligible participants will be generated from the above process and sent to the person in charge of the randomization process.

After the randomization process, the study nurse will receive from the data center the list of the 150 participants selected, who will be invited to participate in the clinical trial. The nurse will call them on the pone for a face-to-face appointment where the details of the study will be informed, doubts will be clarified, and the informed consent form will be signed; a copy of the form will be given to the participant.

During that appointment, the collection of demographic and clinical data will take place, as well as a blood simple for further measurement of VD, lipid profile and glycaemia; the anthropometric nutritional, dietary and physical activity assessment will also be carried out. Once the baseline measurements are taken, the assignment to the intervention will be made in real time through software designed for the study.

Finally, the supplementation intervention will be explained in detail and the package corresponding to the participant's code will be delivered according to the process of assignment to the group (intervention/control), it will be clarified that the supplementation will last 15 weeks and then the second meeting will be scheduled to carry out again the measures taken at the beginning of the study. At the end, a third meeting will be scheduled for the delivery of results and recommendations.

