### Follow-up

3.7

Follow-up will be done 15 weeks after the start of the study (after the end of the intervention).

In addition, all participants will be followed up with a telephone call at weeks 1, 2, 5, 7, and 12. These calls will inquire about any “potential” adverse effects related to the intervention and assess adherence to DV sampling by means of a self-reporting instrument (Table 1).

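### Section 3.11 declares intention to treat but names only tests that need both values of a person; the longitudinal model it mentions in passing should be the main analysis

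*Protocol article*

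**What the plan says.** Section 3.11 (Statistical analysis) opens with the principle: "An analysis will be made by intention to treat". It does not define the analysis set further. For the outcomes it then says: "Quantitative outcome variables will be contrasted through paired t-tests or Wilcoxon tests for quantitative variables", and "for categorical ones the Mc Nemar test will be used". Between these two it adds that "methods of longitudinal data analysis will also be explored", without naming a model.

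On measurement, section 3.5 (Recruitment) takes all outcome measures at the first appointment, before treatment is assigned, and adds that "the second meeting will be scheduled to carry out again the measures taken at the beginning of the study". Section 3.7 (Follow-up) places that repeat at 15 weeks. It also says that "all participants will be followed up with a telephone call at weeks 1, 2, 5, 7, and 12", but those calls ask about adverse effects and adherence and yield no BMI, lipid or 25(OH)D value.

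Section 3.3 (Sample size) includes "a 20% adjustment for losses to follow-up" in the calculation that gives 270. The number is then set at 150, 75 per arm, on feasibility grounds.

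**The concern.** Intention to treat means that every randomised person counts in the arm assigned. A paired t-test, a Wilcoxon signed-rank test and a McNemar test each need two values from the same person. With one post-baseline measurement, a person who misses week 15 has one value and contributes nothing to any of them. Followed as written, the named tests therefore run on complete pairs, while the result would be reported under the intention-to-treat label.

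What is at stake is the protection that randomisation gives. If the people not seen at week 15 differ in their change from those who are seen, and do so unequally between arms, the arms analysed are no longer comparable. The Discussion says that positive results would support recommending supplementation, so the label on the main result matters.

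**Working it through.** **Inputs.** From the article: 150 participants, 75 per arm; a 20% loss allowance; one post-baseline outcome visit; baseline measured before assignment. Assumed here, because the article gives neither: that the 20% applies to the 150, and the size of d, the mean change in people seen at week 15 minus the mean change in people not seen, in SD of change.

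**1. The plan's own figure.** The 270 cannot be reproduced from the stated inputs alone, because no event rates are given. With assumed rates of 20% and 40%, two-sided 5% and 90% power:

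n = [1.960 × √(2 × 0.30 × 0.70) + 1.282 × √(0.20 × 0.80 + 0.40 × 0.60)]² / 0.20² ≈ 108.2, so 109 per arm.

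Inflating for loss gives 109 / 0.80 = 136.25, so 137, or 109 × 1.20 = 130.8, so 131, against 135 stated. Other assumed pairs do not fit: 30% and 50% give 124, then 155. The 270 is plausible but not verifiable. What matters here is that its loss adjustment treats lost participants as supplying no outcome information.

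**2. How many would be left out.** 0.20 × 150 = 30, or 15 per arm. That leaves 60 per arm, 120 in all.

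**3. Precision.** For a between-arm difference of 0.5 SD (assumed), power is 86.5% with 75 per arm and 78.2% with 60.

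**4. Bias.** If a fraction p of an arm is unseen, the full-arm mean change equals the observed mean minus p × d, so the observed mean is off by p × d. The between-arm contrast is off by p₁d₁ − p₀d₀.

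| Loss, intervention / control | d, intervention / control (SD) | Bias in contrast (SD) |
|---|---|---|
| 20% / 20% | 0.5 / 0.5 | 0.10 − 0.10 = 0 |
| 20% / 20% | 0.5 / 0 | 0.10 − 0 = 0.10 |
| 30% / 10% | 0.5 / 0.5 | 0.15 − 0.05 = 0.10 |
| 20% / 20% | 0.25 / 0 | 0.05 |
| 20% / 20% | 1.0 / 0 | 0.20 |

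For scale, the standard error of a difference with 60 per arm is √(2/60) = 0.18 SD, so 0.10 SD is about 0.55 standard errors. With no true effect, that would raise a two-sided 5% error rate to about 8.5%.

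**5. What the longitudinal model changes.** Because baseline precedes assignment, every randomised person should have a baseline value and can enter a model with baseline and week 15 as responses. Complete-pair tests need loss to be unrelated to change within an arm. The model allows loss to depend on arm and baseline. It does not correct for loss that depends on the unseen week-15 value itself.

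**The case against.** The strongest reply is that the article contains no contradiction. A reader might infer that people who stop the capsules are dropped. The documents do not support this: no section withdraws anyone for stopping, the second meeting is scheduled when the package is handed over, and the calls go to all participants. Someone who stops but attends week 15 is analysed in the assigned arm.

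A reader might also infer that the analysis is bound to be one of completers only. That goes too far as well. The article does not say that missing values will be left unfilled, and an imputation rule may stand in a full protocol or analysis plan that is not shown. Its absence from a condensed article is no fault.

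Two further replies are correct. Pairing is not the cause of the loss, since a two-sample test at week 15 would lose the same people. And a baseline-only participant says little about change, so the model gains less than the phrase *everyone stays in* suggests.

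What this does not answer is that the article made a choice. It named the outcome tests, and as named they use complete pairs. The method better suited to the stated principle appears only as an unspecified extra.

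**Conclusion.** The point holds as a poor choice of main method, not as a proven contradiction. The stated tests leave out about 30 of 150 randomised participants if the planning allowance for loss is carried over to the reduced sample. The article does not itself forecast that loss for the 150.

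A reader might take 0.05 to 0.20 SD as the expected bias. It is not. Those values rest on an assumed d from 0.25 to 1.0 SD and on a 20% loss that is informative in one arm only. With equal loss and equal d in both arms the bias is zero, and only precision suffers. The 0.10 SD case is an illustration.

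The change is still worth making. The better method is already mentioned in the same section, needs no new visit, and also supplies an arm-by-visit contrast. The named paired tests compare before with after within an arm and do not give that contrast.

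**What to change.** In section 3.11:

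1. Make the longitudinal model the main analysis. Use baseline and week 15 as responses and the arm-by-visit term as the treatment contrast, with all randomised participants in their assigned arm. The primary outcomes in section 3.9 are measured quantities, so one form of model serves them all.
2. Add one sensitivity analysis that shifts the missing week-15 values over a stated range, separately by arm. At 20% loss, a shift of 0.5 SD in one arm moves the contrast by 0.20 × 0.5 = 0.10 SD, so readers can see how large a departure the conclusion survives.
3. If the paired t, Wilcoxon and McNemar tests are kept, present them as secondary, complete-case descriptions within each arm and not as the intention-to-treat result.

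The cost is revised wording and a little more analysis work; the data needed are already to be collected. The limit should be stated openly: with one follow-up value, baseline-only participants add little information, and the model does not remove loss related to the unseen outcome. That is why the sensitivity analysis is needed.

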### Outcomes

3.9

*Primary outcome:* These are biochemical and anthropometric measurements that allow to respond to the purpose of the study. These include:

Total BMI. This requires taking the size in meters (m) and weight in kilograms (kg).Lipid profile: Measurements will be made of the serum levels of total cholesterol, low-density lipoprotein (LDL), high-density lipoprotein (HDL), and triglycerides.Serum levels of 25(OH) D.

*Secondary outcomes:* These are complementary measurements for the primary outcomes.

Waist-hip ratio: determines the intra-abdominal fat levels and is obtained by dividing the waist perimeter by the hip perimeter.Skin folds: These are taken for the indirect estimation of body fat percentage by means of measuring the bicipital, tricipital, abdominal, and subscapular folds.Fasting glycemia.

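### Section 3.11 lets a Shapiro-Wilk result choose mean or median, and by implication t-test or rank test, so no single effect measure is fixed for BMI, lipids or 25(OH)D

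*Protocol article*

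**What the plan says.** The rule is in section 3.11 (Statistical analysis). Quantitative variables that pass a Shapiro-Wilk check for normality "will be reported as mean and standard deviation, otherwise the median and interquartile range will be presented". The same section offers "the Student's t-test or Mann-Whitney's U-test" for the baseline comparison.

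For the outcomes it says "Quantitative outcome variables will be contrasted through paired t-tests or Wilcoxon tests for quantitative variables", and adds that "methods of longitudinal data analysis will also be explored". Neither of the sentences on tests says how to choose between its two options.

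The primary outcomes in section 3.9 are BMI, four lipids ("Measurements will be made of the serum levels of total cholesterol, low-density lipoprotein (LDL), high-density lipoprotein (HDL), and triglycerides") and 25(OH)D. All are quantitative, so the reporting rule applies to each of them.

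**The concern.** The normality test is the only selection criterion in section 3.11, so it is the natural rule for both choices: mean or median, and t-test or rank test. The first link is written; the second is implied.

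A mean and a median answer different questions, as do a t-test and a rank test. If the data decide which is used, the reader cannot know in advance what a result for BMI or LDL will estimate. At 60 to 75 per arm, Shapiro-Wilk can react to mild departures from normality that do no harm to a comparison of means. Where skew is real, as is plausible for triglycerides, the rule leads to medians and ranks rather than to a log scale, which would keep an estimate with a confidence interval.

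The section does not say whether normality is judged per arm, on the pooled data, per visit or on the change. If it is judged per arm, one arm could be summarised by a mean and the other by a median, and these cannot be subtracted.

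**Working it through.** The plan states no figure on this point, so there is none to reproduce. The check asks how often the rule would split the arms, what it does to error and power, and what a prespecified analysis would gain.

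**Inputs**
- From the documents: 75 per arm and 20% loss to follow-up (section 3.3), so 75 × (1 − 0.20) = 60 per arm analysed; tests at 0.05 (section 3.11).
- Assumed, because the documents give no distributions or variances: Shapiro-Wilk at 5%; log-normal triglycerides with log-SD 0.3-0.5 and visit correlation 0.5-0.7; symmetric t-distributed changes with 4-10 df; for power, log-SD 0.4, correlation 0.5 and a 15% reduction.

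**1. How often two identical arms split, if each is tested separately.** If each arm is rejected with probability p, the arms disagree with probability 2p(1 − p).
- Normal data, p = 0.05: 2 × 0.05 × 0.95 = 0.095. Simulation gives 0.097 at 75 per arm and 0.087 at 60.
- Triglyceride change, p about 0.19 to 0.56: 2 × 0.19 × 0.81 = 0.31, rising to a maximum of 0.50 at p = 0.5. Simulation gives about 0.32 to 0.50.
- Symmetric heavy tails: 0.28 with 10 df, 0.48 with 5 df and 0.50 with 4 df.
- Strongly skewed raw values (log-SD 0.5): only 0.03 to 0.07, because both arms are almost always rejected.

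If normality is judged once per variable, the arms cannot split.

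**2. Type I error.** A between-arm test chosen by Shapiro-Wilk (t-test, or Mann-Whitney if either arm is rejected), 60 per arm, over normal, t with 5 df and log-normal data: 4.8% to 5.2%. The fixed tests gave 4.6% to 5.1%.

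**3. Power for a 15% triglyceride reduction, 60 per arm.**

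| Analysis | Power |
|---|---|
| Shapiro-gated test on raw change | about 53% |
| Fixed t-test on raw change | about 52% |
| Fixed Mann-Whitney on raw change | about 53% |
| t-test on log change | about 60% |
| Raw scale, baseline-adjusted | about 68% |
| Log scale, baseline-adjusted | about 72% |

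Repeated runs differ by a point or two.

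The log-scale rows can be checked by hand with power ≈ Φ(δ/SE − 1.96), where δ = −ln(0.85) = 0.1625.
- Change: SD = 0.4 × √(2 × (1 − 0.5)) = 0.40; SE = 0.40 × √(2/60) = 0.0730; Φ(2.225 − 1.96) = 0.60.
- Baseline-adjusted: SD = 0.4 × √(1 − 0.5²) = 0.346; SE = 0.346 × √(2/60) = 0.0632; Φ(2.57 − 1.96) = 0.73, slightly above the simulated value because the formula uses the normal rather than the t distribution.

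**4. Where the gain comes from.** Baseline adjustment on the raw scale: 68 − 53 = 15 points. Log scale on top of that: 72 − 68 = 4 points (4 to 5 across runs). Taken in the other order, the log scale gives 60 − 53 = 7 points and adjustment 72 − 60 = 12. Adjustment is the larger part either way.

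**The case against.** The strongest reply is that the Shapiro-Wilk sentence concerns description. It sits among the sentences on summarising variables, and the sentence on outcome tests does not mention it. That is fair: the link to test choice is an inference. What stands is that the reporting rule is explicit and covers every primary outcome, and that no other rule exists for picking the test.

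Second, the text speaks of variables, not of variables within arms, so a split between arms is something the wording permits and not something it prescribes. This also stands, and the split rates are conditional on per-arm testing.

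Third, the outcome tests named are paired and hence within-arm. The lack of a between-arm estimate comes mainly from that choice, which is a separate and larger fault; deleting the normality rule alone would not supply an estimate. This stands too. But repairing the paired tests while keeping the rule would still leave the effect measure to be chosen from the data.

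Fourth, transformations and covariates are often left to an analysis plan, and this is a condensed article on a pilot. That would answer a complaint of silence. Here the article itself writes down a data-driven rule, and an analysis plan that followed it would carry it forward.

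A reader might also infer that pre-testing inflates the false-positive rate, or that it costs some 20 points of power (about 52% against 72%). The calculations support neither. Error stays near 5%, and the gated test matches either fixed test on the same scale; the contrast reflects baseline adjustment first and the log scale second.

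**Conclusion.** The point holds in a limited form. Section 3.11 lets the data choose the summary for every primary outcome, and by implication the test, so no single effect measure is fixed. The harm is a result whose meaning is not settled in advance, and the loss of a better prespecified analysis. It is not an error-rate problem, and the pre-test itself costs no power.

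The size depends on assumptions. A split between arms in roughly 30-50% of trials requires per-arm testing and mild skew or heavy tails; it is about 10% under normality and lower still when skew is strong enough that both arms are rejected. The rise from about 53% to 68% and then 72% belongs to one assumed triglyceride scenario. Whether normality is judged per arm should be treated as unknown.

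This should be changed, but it ranks below the use of paired tests for the outcomes.

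**What to change.** In section 3.11:
- Drop the normality test as a decision rule.
- For BMI, total cholesterol, LDL, HDL and 25(OH)D, prespecify the between-arm difference in means at week 15 with a 95% CI, adjusted for the baseline value.
- For triglycerides, prespecify the same comparison on the log scale, reported as a ratio of geometric means with a 95% CI.
- Keep a rank test only as a named sensitivity analysis.
- Report the same summary statistics for both arms and both visits; giving mean (SD) and median (IQR) together would do.

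The cost is a few sentences of text. The baseline and week-15 measurements are already planned, so no further data or resources are needed. The same edit can replace the paired outcome tests with a between-arm comparison.

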### Randomization and blinding

3.4

The randomization process will take place in 2 stages. An engineer from the data central will conduct the randomization of the list of the 217 potentially eligible participants by means of a computer program with random numbers and it will select 150 individuals to participate in the study. Subsequently, a nurse will make phone calls to schedule appointments and formalize the participation in the study, the signature of the informed consent, and the taking of baseline measures. Once these stages are concluded, the assignment of treatment in real time will be made with the support of a computer program. The procedure will take place by means of a single assignment sequence that determines the assignment code for each participant's treatment. This process allows all participants in the study to be assigned to any of the treatment groups. The intervention group will receive 1000 IU of VD while the control group will receive 200 IU of VD.

Supplements will be packaged in individual packages with the total number of doses per participant (105 doses). The coding of the packages will be in charge of the laboratory in charge of providing the supplements, which in turn will send to the designated person at the data center by institutional e-mail, a document with the list of codes and the dose of the supplement.

The 1000 IU and 200 IU doses of VD will be provided in white containers and will be identical in terms of physical and organoleptic characteristics, to ensure that both participants and investigators are blinded to the treatment. To maximize adherence to the intervention, participants will be required to cross out daily supplementation on a calendar with the study period, which they will be required to return at the end of the study.

The results of the assignment will only be known by the systems engineer at the data center. In other words, this information “will not be visible” to the coordinating nurse, laboratory personnel in charge of processing biological samples, pediatrician, principal investigator of the study, or the epidemiologist in charge of quality control and data analysis. This will ensure the masking of the people in charge of measuring the outcomes, administering the intervention and analyzing the study data.

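### Section 3.11 fixes paired before/after tests for the quantitative outcomes; the main analysis should be a between-arm comparison at week 15 adjusted for the baseline value, which is already collected

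*Protocol article*

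**What the plan says.** Section 3.9 (Outcomes) lists BMI, four lipid measures and serum 25(OH)D as primary, which makes six quantitative outcomes. Section 3.5 (Recruitment) places their first measurement at the enrolment appointment, before assignment: "a blood simple for further measurement of VD, lipid profile and glycaemia; the anthropometric nutritional, dietary and physical activity assessment will also be carried out". The same section repeats these measures once, at the second meeting after 15 weeks.

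Section 3.11 (Statistical analysis) uses the baseline data in two ways. For the arms at baseline: "The comparison of the basal characteristics of the study groups (intervention and control) will be done using the ratio comparison test", together with Student's t or Mann-Whitney for quantitative variables. For the outcomes: "Quantitative outcome variables will be contrasted through paired t-tests or Wilcoxon tests for quantitative variables, methods of longitudinal data analysis will also be explored". McNemar's test is given for categorical outcomes. Since Mann-Whitney is named separately, Wilcoxon beside the paired t-test reads as the signed-rank test.

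Section 3.4 (Randomization and blinding) describes allocation thus: "The procedure will take place by means of a single assignment sequence that determines the assignment code for each participant's treatment". The article describes no balancing on baseline values.

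**The concern.** With one baseline and one follow-up measurement, the question in section 2 is answered by a difference between arms at week 15. The tests named in section 3.11 compare each participant with himself or herself. Both arms receive vitamin D, so both may change, and a significant change in one arm but not in the other does not measure the effect of the higher dose.

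The simplest repair that stays close to the text would be a two-sample test on the before/after differences. That fixes the coefficient of baseline at 1 instead of using its regression slope. The interval is wider than it need be, and if the arms happen to differ at baseline, part of that difference passes into the estimate. Testing the baseline values for significance does not remove it. Precision is scarce here, because section 3.3 reduces a calculated 270 participants to 150 for feasibility.

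**Working it through.** **Inputs from the article (section 3.3).** Planning parameters: "a power of 90%, an alfa of 5%, an intervention group/control group ratio of 1:1, and a 20% adjustment for losses to follow-up". Target: "an expected difference in the study outcomes (overweight, obesity, and alteration of the lipid profile) of 20% between the intervention group and the control group". Result: "resulting in a sample of 270 participants (n = 135 intervention and n = 135 control group". Size adopted: "the research team decided on a sample size of 150 participants (n = 75 intervention group and n = 75 control group". Applying the plan's own 20% loss to the adopted size leaves 75 × 0.8 = 60 per arm.

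**Assumed.** The correlation ρ between baseline and week 15 (range 0.3 to 0.9), equal SDs at the two times, effects in SD units, and two-sided 5% tests. The article gives no ρ and no SD.

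**The plan's own figure.** The 135 per arm cannot be reproduced uniquely because no control proportion is stated. For two proportions, 40% against 20% needs 109 per arm, and 109/0.8 = 136.25, so 137. With a continuity correction, 35% against 15% needs 107, and 107/0.8 = 133.75, so 134. But 50% against 30% needs 124, and 124/0.8 = 155. The stated figure is therefore compatible with some control rates and is not shown to be wrong. It concerns proportions, so it fixes no detectable difference for the six continuous outcomes.

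**What paired tests can show.** Suppose both arms change equally by 0.2 SD, with ρ = 0.7 and 75 per arm. Each paired test is significant with probability 0.609. The chance that exactly one arm is significant is 2 × 0.609 × 0.391 = 0.476. In almost half of such trials the two arms would appear to disagree although the doses do not differ in effect.

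**Variance of a between-arm difference.** With n per arm it is (2σ²/n) × k:

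- week-15 value alone: k = 1
- change score: k = 2(1−ρ)
- ANCOVA: k = 1−ρ²

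Change score minus ANCOVA is 2(1−ρ) − (1−ρ²) = (1−ρ)², which is positive for every ρ below 1. The proportion of variance saved against the change score is (1−ρ)²/[2(1−ρ)] = (1−ρ)/2.

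| ρ | k, change score | k, ANCOVA | variance saved |
|---|---|---|---|
| 0.3 | 1.40 | 0.91 | 35% |
| 0.5 | 1.00 | 0.75 | 25% |
| 0.7 | 0.60 | 0.51 | 15% |
| 0.9 | 0.20 | 0.19 | 5% |

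**Illustrative power.** Take a true difference of 0.3 outcome SD, chosen only for illustration, and the normal approximation. With 75 per arm, change score against ANCOVA gives 34% and 49% at ρ = 0.3, 45% and 56% at 0.5, 66% and 73% at 0.7, and 98% and 99% at 0.9. With 60 per arm and ρ = 0.7 it is 56% and 63%.

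**Chance imbalance.** The standard error of the baseline difference between arms is √(2/n) SD: √(2/75) = 0.16 and √(2/60) = 0.18. The 95% ranges are ±0.32 and ±0.36 SD. Given an observed baseline difference δ, the expected difference in change is displaced by −(1−ρ)δ. For δ = 0.2 SD the displacement is 0.14 SD at ρ = 0.3, 0.10 at 0.5, 0.06 at 0.7 and 0.02 at 0.9. ANCOVA removes it when the linear model holds.

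**The case against.** The strongest reply is that a journal article condenses the protocol, and covariates are commonly left to the statistical analysis plan. Silence about a covariate would indeed be no finding. But section 3.11 is not silent: it selects paired tests as the outcome analysis, and that choice is the point.

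Three further parts of the opposing case stand and limit what can be said.

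- A reader might infer that the baseline is never used except in paired tests and a baseline table. The text does not support that. It leaves room for longitudinal methods, which could condition on baseline. They are only to be explored, however, and have no stated model or standing.
- A reader might infer that the planned analysis loses a known amount of power or carries imbalance in its estimates. As written, it contains no between-arm estimate from which power could be lost. The loss belongs to a change-score comparison, should that be the repair chosen. The covariate question is thus tied to the absence of a between-arm outcome comparison, and one amendment settles both.
- A reader might infer that a difference in change is biased. Under randomisation it is unbiased on average, because regression to the mean is expected equally in both arms. Only the bias conditional on an observed imbalance remains.

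The size is also open to challenge. One can convert section 3.3 to a standardised difference (90% power at 135 × 0.8 = 108 per arm gives 0.44), which yields 67% power at 60 per arm, rising to 79% with adjustment at ρ = 0.5. But section 3.3 addresses categorical outcomes, and those figures depend on the assumed ρ. They are not the plan's power for BMI, lipids or 25(OH)D.

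**Conclusion.** The point holds in a limited form. Section 3.11 fixes within-person tests for six quantitative primary outcomes, and these give no 1000 against 200 IU estimate. No stated model uses the baseline as a covariate, although every baseline value is collected before assignment.

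That adjustment is at least as efficient as a change score follows from the algebra for any ρ below 1, apart from one degree of freedom. The size of the gain does not follow from the article: 5% to 35% of variance for ρ from 0.9 down to 0.3, assuming equal SDs. If ρ is 0.9 or more, as is plausible for BMI over 15 weeks, the gain over a change score is small. It is material for any lipid or 25(OH)D measure whose ρ lies between 0.3 and 0.7. All power figures are illustrative. The amendment is worth making because it improves a stated method at almost no cost.

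**What to change.** In section 3.11, replace the paired t and Wilcoxon tests as the main analysis of each quantitative outcome with a linear model (ANCOVA): week-15 value as response, with arm and the same variable's baseline value as explanatory terms. Report the adjusted difference, 1000 minus 200 IU, with its 95% confidence interval. State that the baseline covariate is included for every outcome, whatever the baseline comparison tests show. Keep within-arm paired changes as description only. If longitudinal methods are retained, name the model and say that it is supplementary.

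Cost: a few sentences and one degree of freedom per model. No new data, visits or participants are needed.
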